### Plans to give access to the full protocol, participant level-data and statistical code {31c}

No later than 3 years after the end of the trial, we plan to deliver a completely de-identified data set to an appropriate data archive for sharing purposes.

## Oversight and monitoring

### Composition of the coordinating center and trial steering committee {5d}

The coordinating study center is the Department of Otolaryngology, Jena University Hospital. The trial steering committee (TSC) consists of members of the Jena University Hospital, Germany, of the clinical trial center, University Medical Center, Göttingen, Germany, and the lead investigators in each participating study center. The Trial Management Committee (TMC) consists of the chief investigator, members of the BVHNO, the DGHNO-KHC, and of the clinical trial center, University Medical Center, Göttingen, Germany. The TMC was responsible for all aspects of the study planning, and will be responsible for the randomization, data registration, pharmacovigilance, data management, biostatistics and study monitoring. The TMC also organizes the TSC meetings.

### Composition of the data monitoring committee, its role and reporting structure {21a}

An independent data monitoring committee (DMC) is established. The DMC can make recommendations independent of the sponsor, the coordinating study center, or of the TSC. The function of the DMC is to check predefined data sets and data points in a defined frequency and to assess whether, on the one hand, study participant safety is still guaranteed and whether, on the other hand, the conduct of the study is still ethically responsible and whether the fundamental benefit assessments have shown changes. The TOTO DMC charter will describe the composition, the tasks, the organizational structure, the review, and decision-making processes as well as the reporting to and by the DMC in detail. The DMC charter will be available on request from the TSC.

### Adverse event reporting and harms {22}

An adverse event (AE) will be defined as any untoward medical occurrence in a participant without regard to the possibility of a causal relationship. AEs will be collected after the participant has provided consent and enrolled in the study. If a participant experiences an AE after the informed consent document is signed (entry) but the participant has not started to receive study intervention, the event will be reported as not related to the intervention. All AEs occurring after the entry into the study and until discharge from the study will be recorded. After discharge from the hospital, i.e., during the follow-up phase at home, the participants are asked to report AE at least during the weekly app consultation. An AE that meets the criteria for a serious adverse event (SAE) between study enrollment and discharge will be reported to the local Ethics committee and the sponsor as an SAE. If the tonsil surgery is discontinued as a result of an AE, study personnel will document the circumstances and data leading to the discontinuation of treatment. A SAE for this study is any untoward medical occurrence that is believed by the investigators to be causally related to study intervention and results in any of the following: life-threatening condition (that is, immediate risk of death); severe or permanent disability, prolonged hospitalization, or a significant hazard as determined by the DMC. SAE occurring after a participant is discontinued from the study will NOT be reported unless the investigators feel that the event may have been caused by the study drug or a protocol procedure. Investigators will determine the relatedness of an event to study intervention based on a temporal relationship to the study intervention, as well as whether the event is unexpected or unexplained given the subject’s clinical course, previous medical conditions, and concomitant medications.

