#### Secondary outcomes measures

The number of symptomatic sore throat episodes within the first 12 monthsThe number of days of incapacity for work/inability to go to the kindergarten/school and sore throat related limitation in daily routine cumulated at 6, 12, 18, and 24 monthsTonsil and Adenoid Health Status Instrument (TAHSI) and the Tonsillitis Outcome Inventory-14 (TOI-14) prior and after surgery at 6, 12, 18, and 24 months [9–11]Quality of life assessed by Short Form-12 (SF-12) Questionnaire prior to surgery and after surgery at 6, 12, 18, and 24 months [12]Cumulative number of days using analgesics because of sore throat within 24 monthsCumulative number of days using antibiotics because of sore throat within 24 monthsSafety analyses: morbidity and mortality after surgery, primary/secondary bleedings within 24 months; intraoperative and postoperative complicationsRevision tonsil surgery within 24 months

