Several quality assurance measures will take effect at various levels to meet the quality of the data collected but also the requirements of the ICH GCP (as a reference system). At the implementation level, quality assurance will be carried out in accordance with the existing SOPs of the study center in Göttingen, Germany. This includes, among other things, that pre-study visits and initiation visits take place before the centers open and that the monitoring would be implemented according to a study-specific monitoring plan. As part of a risk-based management approach, risk-adapted monitoring and project management strategies will come into play. The data will be collected via a separate eCRF system (SecuTrial). This system uses a specific role concept with different authorizations for centers, monitors, and data managers. All data entries including deletions and changes can be tracked via an audit trail. Automatic checks for plausibility and correctness of the data will be implemented. Query management for questionable data entries is performed. The database is validated before commissioning. The database is not closed until the database is cleaned up.

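### The SAE definition depends on an unblinded causality judgement and lists neither death nor new hospitalization, so some serious events can bypass SAE reporting to the sponsor and ethics committee

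*Protocol article*

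**What the plan says.** All the safety definitions are in the protocol article, section Adverse event reporting and harms {22}.

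- An AE is "any untoward medical occurrence in a participant without regard to the possibility of a causal relationship".
- An SAE is narrower: "A SAE for this study is any untoward medical occurrence that is believed by the investigators to be causally related to study intervention", with one of these results: "life-threatening condition (that is, immediate risk of death); severe or permanent disability, prolonged hospitalization, or a significant hazard as determined by the DMC".
- The reporting rule reads: "An AE that meets the criteria for a serious adverse event (SAE) between study enrollment and discharge will be reported". The recipients are the local ethics committee and the sponsor.
- Relatedness is decided by the investigators, "based on a temporal relationship to the study intervention, as well as whether the event is unexpected or unexplained" in view of the participant's course, history and medication.
- For participants who have left the trial, "SAE occurring after a participant is discontinued from the study will NOT be reported unless the investigators feel" that a study drug or a protocol procedure may have caused the event.

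Three other sections bear on this. The blinding section {17a} says that the otolaryngologists involved are not blinded. The secondary outcomes include "morbidity and mortality after surgery, primary/secondary bleedings within 24 months", together with complications and revision surgery. The participant timeline {13} leaves day care open for tonsillotomy and makes tonsillectomy always in-patient, yet it also gives every patient a ward stay of at least 3–5 days.

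**The concern.** Whether an event is serious and whether surgery caused it are separate questions. The AE definition keeps causality out, but the SAE definition makes causality a condition of entry. An investigator who thinks an event unrelated therefore removes it from SAE reporting altogether, when it could have been reported with relatedness marked as no. That investigator knows which operation was done.

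The list of criteria adds to the problem. The Background section cites deaths from severe bleeding after tonsillectomy in children as the reason why tonsillotomy was promoted in Austria, and the trial was commissioned because long-term benefits and risks were unclear. Yet death is not a listed criterion, and hospitalization counts only when prolonged. What is at stake is whether the sponsor and ethics committee are told of such events as SAEs, and whether a count of SAEs by arm would mean the same thing in both arms.

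**Working it through.** No arithmetic applies. The article gives no SAE, bleeding, readmission or death rate, so the check is a reading of the rules against each other and against plausible events.

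**1. Structure of the definition.** An SAE needs (a) causality as believed by the investigators and (b) one of four results: life-threatening condition, severe or permanent disability, prolonged hospitalization, or a DMC-determined hazard. Condition (a) governs all four, so the DMC item cannot bring in an event judged unrelated.

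**2. Events tested against it.**

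| Event | (a) Related? | (b) Listed result? | SAE as written? |
|---|---|---|---|
| Death judged unrelated | No | Death not listed | No |
| Fatal bleed judged related | Yes | Probably, as life-threatening | Probably yes |
| Other serious event judged unrelated | No | Irrelevant | No |
| Readmission for late bleeding, related, life-threatening | Yes | Yes | Yes, if inside the window |
| Readmission for late bleeding, related, not life-threatening | Yes | A new stay rather than a prolonged one; only the DMC item remains | Not unless the DMC classes it as a hazard |

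**3. The window.** SAE reporting runs from enrollment to discharge. The same section uses discharge in two senses: from the study, where it says how long AEs are recorded, and from the hospital, where it describes follow-up at home. The SAE sentence does not say which is meant. If it means the hospital, every bleed at home falls outside SAE reporting, although bleeding is a safety outcome to 24 months.

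**4. Consistency within the section.** The rule for participants who have left the trial admits an SAE only if the intervention may have caused it. If every SAE is already believed to be caused by the intervention, this rule filters nothing. It has work to do only if SAEs can be unrelated, so the two sentences imply different definitions. The rule also names a study drug, which a trial of two operations does not have.

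**5. Baseline for prolonged hospitalization.** The day-care option would give the arms different baselines, and the 3–5 day ward stay for everyone would give them the same minimum. Both statements are in the participant timeline {13} and they conflict, so the baseline is undefined.

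**6. What is still captured.** AEs are recorded regardless of causality until discharge from the study. Table 1 schedules complications and AEs at surgery, on postoperative days 1–5, weekly to month 24 and at close-out. Mortality, bleeding, complications and revision surgery are secondary outcomes that do not depend on the SAE label. The safety population is everyone operated on.

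**The case against.** The strongest reply is that the comparison of harms does not rest on the SAE label. A late bleed or an unrelated death is still recorded and still enters the safety outcomes. This stands. A reader might infer that the comparison of harms between the operations is biased by the SAE wording, and the document does not support that.

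Two other strong readings also fail. One is that all deaths escape SAE reporting. A fatal bleed judged related would probably qualify as life-threatening, and timing is one of the stated grounds for relatedness, so a bleed soon after surgery would be hard to call unrelated. The other is that events escape unequally by arm. Open-label judgement and a possible difference in care setting make this conceivable, but the ward-stay statement points to an equal minimum stay, and nothing in the document fixes a size or direction.

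It can also be said that a broad AE definition and a narrower SAE definition may coexist. That is so, and the difference alone is no contradiction. The data management section refers to "the requirements of the ICH GCP (as a reference system", but in a paragraph on data quality and without an SAE definition, so this point does not rest on it.

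Finally, the full protocol and the DMC charter are not shown. They may contain further reporting routes, but the article states its SAE rule outright, and a stated rule can be judged as stated. The reference to a study drug is leftover wording and carries little weight by itself.

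**Conclusion.** The concern holds as a defect in SAE classification and in reporting to the sponsor and ethics committee. As written, two groups of events can escape: serious events judged unrelated, including deaths, and readmissions that are neither life-threatening nor classed by the DMC as a significant hazard. If discharge means leaving hospital, all later SAEs are added. Any comparison of SAEs by arm would inherit an unblinded relatedness filter, which is a possible bias and not a demonstrated one.

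The number of events cannot be computed, because no rates are given. The conclusion assumes that sites apply the SAE definition literally and that the full protocol does not replace it with a different one. It does not extend to loss of harm data or to the secondary safety outcomes. The change should be made because it serves participant safety at little cost.

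**What to change.** In the section on adverse event reporting and harms {22}:

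- define seriousness independently of relatedness;
- list death and new or prolonged hospitalization among the criteria;
- record relatedness as a separate field on the SAE form;
- state that the SAE window runs from consent to the end of the 24-month follow-up;
- revise the rule for participants who have left the trial so that it agrees with the new definition, and refer there to the study intervention in place of a study drug.

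In the participant timeline {13}, reconcile the day-care and 3–5 day ward statements, so that prolonged hospitalization has a defined baseline.

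The cost is a change of protocol and eCRF wording and some additional SAE forms. Treatment, sample size and endpoints are unchanged.

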### Frequency and plans for auditing trial conduct {23}

Monitoring and source data verification are the important parts f the auditing trial conduct independent from investigators and the sponsor.

#### Monitoring

The investigator in each study center grants the monitor access to the participant’s medical records to verify the proper documentation of the study data. The provisions of the Federal Data Protection Act are fully respected. The monitor is bound to the contractual confidentiality regulations when comparing the CRFs with the source documents. All investigators agree that the monitors can visit the study center before, during, and after the study is completed. The investigator must allow enough time for these visits. Alternatively, other trained personnel (e.g., so-called co-examiners) can be made available to the monitor for support during the visits. The reviewer grants the monitor access to the source documents to perform its duty. The aim and purpose of these visits are in particular: assessment of the progress of the study, checking compliance with the study protocol, CRF check for correctness and completeness, and CRF validation and source data comparison. A monitor report is created for each visit. This documents the progress of the study and provides a report on all problems that have occurred (e.g., deviations from the study protocol. The monitor will also hold a contact to the centers by phone between visits.

#### Source data verification (SDV)

The monitoring is also important for the source data check. The source data is checked in order to check the correctness and completeness of the entries in the CRF by comparison with the original data and thus to ensure and improve the quality of the data. All data required for SDV must have been entered in the medical record or, for source documents, in the medical record. The investigators grant the monitor access to the medical documents for performing the source data comparison. The source data defined by ICH-GCP include data such as hospital records, clinical diagrams, patient diaries or evaluation checklists, copies or transcriptions that have been certified as such after verification, exact copies, microfiches, photographic negatives, microfilms or magnetic media, telephone surveys can - after signing off by the examiner - considered as source data.

### Plans for communicating important protocol amendments to relevant parties (e.g., trial participants, ethical committees) {25}

Any modifications to the protocol which may impact on the conduct of the study, a potential benefit of the patient or may affect patient safety, including changes of study objectives, study design, patient population, sample sizes, study procedures, or significant administrative aspects will require a formal amendment to the protocol. Such an amendment will be agreed upon by TSC and the sponsor and approved by the Ethics Committee prior to implementation. The amendments will be notified to the health authorities in accordance with local regulations. Administrative changes of the protocol are minor corrections and/or clarifications that do not affect on the way the study is to be conducted. These administrative changes will be agreed upon by the TSC and the sponsor and will be documented in a memorandum.

### Dissemination plans {31a}

The TSC is responsible for all publications. The scientific integrity of the project requires that the data from all TOTO sites be analyzed study-wide and reported as such. Thus, an individual center is not expected to report the data collected from its center alone. All presentations and publications are expected to protect the integrity of the major objective(s) of the study; data that break the blind will not be presented prior to the release of mainline results. Primary outcome papers in peer-reviewed publications and other study papers, abstracts, and presentations are planned. The study results will be released to the participating physicians, referring physicians, patients, and the general medical community.

## Discussion

TOTO follows a public contract by the G-BA, the highest decision-making body for joint self-government in the German healthcare system. TOTO evaluates if a tonsillotomy is not inferior to a tonsillectomy if tonsil surgery is indicated for recurrent acute tonsillitis. The findings will likely have a high impact on clinical management strategies in Germany and may be beyond Germany. Based on the results, the G-BA will probably decide if tonsillotomy because a standard procedure or alternative to tonsillectomy for the treatment of recurrent acute tonsillitis. Using randomization in this study design, we aim to limit confounders as much as possible. Nevertheless, as the effect of tonsillotomy versus tonsillectomy is obvious to the participant and involved physicians, blinding was not feasible. Therefore, it seems for us to be very important that the involved biostatistician will be blinded until database lock and that the assessment of the primary endpoint and secondary endpoints is following a strict evaluation algorithm. A strength but also a challenge is the long follow-up period of 24 months. To sustain the compliance over such a long period, a concept with only a little interference for the participants/parents was chosen. Visits in the study are not necessary if the follow-up is uneventful. By use of the TOTO app, the follow-up parameters can be delivered within seconds to a few minutes.

Two important issues cannot be solved by the TOTO trial. First, the definition of recurrent acute tonsillitis is mainly based on clinical diagnosis, i.e., has a subjective component. So far, clear objective parameters are missing [15]. Furthermore, the indication for tonsil surgery in case of recurrent acute tonsillitis is internationally seen very controversially. We followed with our very strict inclusion criteria the German clinical guideline [4]. This guideline, in turn, follows the strict criteria based on the milestone publications of Paradise et al. [16, 17]. Second, TOTO compares two methods of tonsil surgery. A comparison to conservative management is not performed. To ask this question, the NAtional randomised controlled Trial of Tonsillectomy IN Adults (NATTINA) study was designed [5]. NATTINA recruitment ended successfully and we look forward to the results. As the TOTO 10-question survey in case of sore throat covers all questions asked also in the NATTINA questionnaire and because NATTINA also used the TOI-14 and the SF-12 as secondary outcome criteria, a common pooled analysis will be feasible. Such a pooled analysis with gain additional information on the comparison of tonsillotomy versus conservative treatment as in NATTINA only tonsillectomy is performed as a surgical method.

## Trial status

Protocol version number: V 1.1; date: 08-May-2020; date of planned recruitment begin:01-September-2020; the approximate date when recruitment will be completed: 01-September 2022.

## Data Availability

The TSC and the investigators will have access to the final trial dataset. We disclose contractual agreements that limit such access for investigators.

## Abbreviations

AE: Adverse event
DMC: Data monitoring committee
eCRF: Electronic case report form
EDC: Electronic data capture
GCP: Good clinical practice
IQWiG: German Institute for Quality and Efficiency in Health Care (Institut für Qualität und Wirtschaftlichkeit im Gesundheitswesen)
G-BA: Federal Joint Committee (Gemeinsamer Bundesausschuss)
IIT: Intention to treat
NRS: Numeric rating scale
PP: Per protocol
SAE: Serious adverse event
SAP: Statistical analysis plan
TAHSI: Tonsil and Adenoid Health Status Instrument
TOI: Tonsillectomy Outcome Inventory
TOTO: Scronym of the trial
TSC: Trial steering committee
